**Fig. 1 Fig1:**
[figure not shown]
Flowchart high FiO_2_ and/or high PEEP

### Strategies to improve adherence to interventions {11c}

At least one blood gas analysis per shift (three per 24 h) will be required while mechanically ventilated.

If a participating ICU has difficulty adhering to the oxygenation targets and there is risk of overlap between the groups, the “aiming point PaO_2_” provides guidance to the bedside clinicians:
Conservative arm aiming point PaO_2_ 60 mmHg (8 kPa)Conventional arm aiming point PaO_2_ 135 mmHg (18 kPa)

### Relevant concomitant care permitted or prohibited during the trial {11d}

Among other concomitant care, sedation, selective oropharyngeal or digestive tract decontamination, thrombosis prophylaxis, fluid regimens, and nutrition follow the local guidelines in each participating ICU and are permitted during the trial.

### Provisions for post-trial care {30}

No provisions or restrictions are applicable for post-trial care. The sponsor has an insurance which is in accordance with the legal requirements in the Netherlands (Article 7 WMO). This insurance provides cover for damage to research subjects through injury or death caused by the study. The insurance applies to the damage that becomes apparent during the study or within 4 years after the end of the study.

### Outcomes {12}

The primary endpoint is all-cause mortality at 28 days after randomization. The secondary study endpoints are as follows:
The number of ventilator-free days and alive at day 28, defined as the number of calendar days from day 1 to day 28, the patient is alive and breathes without assistance of the mechanical ventilator. Ventilator-free days are according to the definitions by the Dutch National Intensive Care Evaluation (NICE) registry [27].ICU length of stay (LOS)Hospital LOSICU mortalityHospital mortality90-day mortalityIschemic events (cardiac, neurological and peripheral)

Follow-up (in participating subjects from the Netherlands):
Quality of life at 6 and 12 monthsPatient opinion of research and consent in the emergency setting at 6 months after randomization

### Participant timeline {13}

Participant timeline is shown in Fig. 2.

**Fig. 2 Fig2:**
[figure not shown]
Schedule of enrollment, intervention, and assessments

### Sample size {14}

Based on an expected mortality in the control group of 24% (source: Dutch NICE foundation; NICE online [27]), we will include 1512 patients to detect an absolute difference in mortality of 6% (2-sided, alpha 0.05, power 80%, similar allocation of subjects to each group and corrected for 4% dropouts). The choice of 6% was motivated by the difference of 8% found in a previous trial [16] comparing conventional to conservative oxygenation targets and what could be considered clinically acceptable.

### Recruitment {15}

All patients admitted to participating ICUs or intubated on participating ICUs will be screened for eligibility.

## Assignment of interventions: allocation

### Sequence generation {16a}

Randomization sequence is generated by a dedicated computer randomization software program (Castor EDC, Amsterdam, The Netherlands) using variable block sizes and is stratified per participating center.

Details of blocking are provided in a separate document that is unavailable to those who enroll participants or assign interventions.

### Concealment mechanism {16b}

Randomization will be performed using a dedicated, password-protected, SSL-encrypted website (Castor EDC, Amsterdam, The Netherlands).

### Implementation {16c}

The allocation sequence is generated by a dedicated computer randomization software program (Castor EDC, Amsterdam, The Netherlands). Patients will be enrolled by local investigators and/or treating physicians in participating ICUs, and the intervention will be randomly assigned by the computer randomization software.

## Assignment of interventions: blinding

### Who will be blinded {17a}

Due to the nature of the intervention, the clinicians and the outcome assessors are not blinded, but the data analysts will remain blinded.

### Procedure for unblinding if needed {17b}

Not applicable, there is no blinding of care providers.

## Data collection and management

### Plans for assessment and collection of outcomes {18a}

Only data needed to assess primary and secondary objectives will be collected in electronic case report forms and extraction from the patient registry systems. Data will be regularly checked on quality, errors, and outliers and corrected if possible.

Two questionnaires are used for the follow-up of subjects from the Netherlands:
EQ-5D [28, 29]A self-developed questionnaire assessing patient opinion and experience of the consent procedure of research in the emergency setting, which is a modified and translated version of the questionnaire used in a previous trial [30].

Subjects will receive these questionnaires per mail or e-mail.

### Plans to promote participant retention and complete follow-up {18b}

No or minimal losses to follow-up for the primary outcome is anticipated. Complete-case analysis will be carried out for all the outcomes. However, if more than 5% of missing data is found for the primary outcome, a sensitivity analysis using multiple imputations will be carried out.

### Data management {19}

All patients will be allocated with a random patient identification code. Patient-identifying data will be omitted. The codebook will be stored digitally and in paper and will be safeguarded by the site investigator. The paper version will be stored behind a lock and the digital form will be encrypted. Source data will be stored at the specific study site where it originated and will be safeguarded by the site investigator. Data sent to the project leader or principal investigator will only contain this code and will not contain patient-identifying information.

### Confidentiality {27}

A codebook of enrolled participants will be collected and stored digitally or in paper, encrypted or behind a lock. The personal information in these files will not be shared with other investigators.

### Plans for collection, laboratory evaluation, and storage of biological specimens for genetic or molecular analysis in this trial/future use {33}

Not applicable, no biological specimens are collected.

## Statistical methods

### Statistical methods for primary and secondary outcomes {20a}

#### Primary outcome

The primary endpoint, all-cause mortality at day 28, is analyzed using Kaplan Meier. The statistical analysis will be based on the intention-to-treat principle, with patients analyzed according to their assigned treatment arms, except for cases withdrawn or without informed consent. The primary outcome will be assessed using a two-sided superiority hypothesis test, with a significance level of 0.05 and presented with two-sided 95% confidence intervals. In addition, we will perform a per-protocol analysis to check for robustness of results. The per-protocol group analysis only considers patients of the conservative group if 50% or more of the PaO_2_s in the blood gas analysis is equal to or below 10.7 kPa (80 mmHg), and patients of the conventional group if 50% or more of the PaO_2_ in the blood gas analysis is equal to or above 14.7 kPa (110 mmHg).

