### Who will take informed consent? {26a}

Informed consent will be obtained according to local legal regulations. Informed consent will be obtained, if possible, prior to start of intervention. However, due to the emergency setting of this trial, this will occur in the minority of subjects. For the majority of subjects, inclusion will take place in an emergency setting when the patient is incapacitated and deferred consent from a proxy will be obtained as soon as possible. Information about the trial will be given by the treating physician to the proxy. After deferred proxy consent is obtained, decisional capacity of the participant will be assessed frequently and when regained during the ICU stay deferred subject consent must be obtained.

If the patient dies before informed consent or deferred (proxy or subject) consent is obtained, the study data will be used. The Dutch central committee of research in humans (Centrale Commissie Mensgeboden Onderzoek (CCMO)) states that legal representation of a patient ends after death and that therefore the obligation to obtain signed consent no longer applies after death of the patient [25].

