### Criteria for discontinuing or modifying allocated interventions {11b}

Subjects can leave the study at any time for any reason if they wish to do so without any consequences. The investigator can decide to withdraw a subject from the study for urgent medical reasons. When deferred consent is not obtained after randomization and provisional inclusion of a patient or when a patient withdraws consent. The replacement of the randomization subject will be done in the automated randomization scheme.

To avoid prolonged exposure to very high inspiratory oxygen concentrations, the allocated intervention can temporarily be modified in the conventional PaO_2_ target group when FiO_2_ is above 80% for more than 2 h and/or PEEP is above 15 cmH_2_O for more than 2 h. In order to provide guidance when clinicians are in a situation with high inspiratory oxygen concentrations, we created a flowchart (Fig. 1).

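### The primary set is called intention-to-treat, but its exclusions can depend on vital status and on knowledge of the arm, and the consent, withdrawal and analysis sections do not agree on who is excluded

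*Protocol article*

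**What the plan says.** Three sections of the protocol article decide who enters the primary analysis.

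- **Primary outcome, under {20a}.** The analysis follows intention-to-treat, "with patients analyzed according to their assigned treatment arms, except for cases withdrawn or without informed consent".
- **Who will take informed consent? {26a}.** Most patients are randomised first, and a proxy is asked at the earliest opportunity: "inclusion will take place in an emergency setting when the patient is incapacitated and deferred consent from a proxy will be obtained as soon as". A second step follows for those who recover: "decisional capacity of the participant will be assessed frequently and when regained during the ICU stay deferred subject consent must be obtained". For deaths before any consent: "If the patient dies before informed consent or deferred (proxy or subject) consent is obtained, the study data will be used".
- **Criteria for discontinuing or modifying allocated interventions {11b}.** "The investigator can decide to withdraw a subject from the study for urgent medical reasons". The same paragraph lists, in an incomplete sentence, "When deferred consent is not obtained after randomization and provisional inclusion of a patient or when a patient withdraws consent", and then adds: "The replacement of the randomization subject will be done in the automated randomization scheme".

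The trial is open-label (Trial design {8}). Clinicians and outcome assessors know the arm, and only the data analysts are blinded (Who will be blinded {17a}).

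Two robustness checks are stated. One is a per-protocol analysis based on achieved PaO2. The other is conditional: "However, if more than 5% of missing data is found for the primary outcome, a sensitivity analysis using multiple imputations will be carried out".

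**The concern.** Under deferred consent, randomisation comes first and permission second. If deaths before consent are kept and living patients without consent are removed, membership of the primary set depends on vital status when consent is sought, and vital status is the primary outcome. Patients who regain capacity in the ICU face a further request that those who die earlier never reach.

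The word "withdrawn" adds a second route. It can mean consent withdrawn, or it can include patients whom the investigator takes out on medical grounds. On the second reading, staff who know the arm can remove patients who may be at raised risk of death, although nothing about consent requires their vital status to be discarded.

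Neither planned check need detect this. Excluded patients need not count as having missing outcomes, so the 5% trigger may never be reached. The per-protocol analysis selects further after randomisation. Replacement restores the number of patients but not the comparability of the arms. At stake are the mortality contrast, the stated 5% type I error and the accuracy of the intention-to-treat label.

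**Working it through.** **1. The sections side by side.** Take a patient randomised under deferred consent who dies before consent is obtained.

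- Under {26a} this patient is analysed.
- Under the literal wording of {20a} this patient has no informed consent and is excluded.

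Both cannot hold. A living patient whose deferred consent is not obtained is excluded under {20a} and, it appears, replaced under {11b}. Either reading ties exclusion to vital status, in opposite directions. The rest of this working follows {26a}, which addresses these deaths explicitly.

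**2. The plan's own figure.** Sample size {14}: 24% versus 18%, two-sided alpha 0.05, power 80%, 4% dropout, total 1512. With pooled variance,

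n per arm = [1.960·√(2·0.21·0.79) + 0.842·√(0.24·0.76 + 0.18·0.82)]² / 0.06² ≈ 722.2, rounded up to 723.

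The total is 1446, and 1446/0.96 = 1506.25, so 1507 (1508 if each arm is rounded up). This is close to 1512, so the figure reproduces. The calculations below use 1512/2 = 756 per arm.

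**3. Assumptions.** True 28-day mortality is p = 24% in both arms, so any difference is spurious. The documents give no exclusion rates; those used here are illustrative. Rejection rates come from a normal approximation to the two-sided 5% comparison of proportions.

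**4. Consent exclusions, upper bound.** Remove a fraction r of day-28 survivors and keep every death:

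observed mortality = p / [p + (1 − p)(1 − r)]

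| r, arm A vs arm B | Observed mortality | Spurious difference | Rejection rate | Share of all patients excluded |
|---|---|---|---|---|
| 3% vs 5% | 24.6% vs 25.0% | 0.4 points | 5.3% | 3.0% |
| 2% vs 6% | 24.4% vs 25.2% | 0.8 points | 6.4% | 3.0% |
| 2% vs 8% | 24.4% vs 25.6% | 1.2 points | 8.2% | 3.8% |
| 8% vs 8% | 25.6% vs 25.6% | 0 | 5.0% | 6.1% |

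Equal exclusion raises absolute mortality but creates no difference under the null.

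**5. Consent exclusions when some deaths follow the request.** Suppose half the deaths (12% of patients) occur before consent is sought and half after. Of the 88% alive when asked, remove a fraction r whatever their later outcome:

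observed mortality = [0.12 + 0.12(1 − r)] / [0.12 + 0.88(1 − r)]

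- r = 2%: 0.2376/0.9824 = 24.19%
- r = 8%: 0.2304/0.9296 = 24.78%

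The difference is 0.6 points, half the upper bound, and the rejection rate is 5.8%. Exclusions are 0.88 × (2% + 8%)/2 = 4.4% of all patients.

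**6. Medical withdrawals.** Remove a share w of one arm whose mortality is m:

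observed mortality = (p − w·m)/(1 − w) = (0.24 − 0.03 × 0.60)/0.97 = 22.9%

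Against 24.0% in the other arm, this is 1.1 points, with a rejection rate of 8.0%. Exclusions are 1.5% of all patients.

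**7. Both together.** Removing survivors raises an arm's observed mortality; removing high-risk patients lowers it.

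- In opposite arms, at the step 4 upper bound: 25.6% versus 23.3%, about 2.3 points. Exclusions are 3.8% + 1.5% = 5.3%, above the planned 4% dropout.
- In the same arm: 24.4% versus 24.4%. The effects cancel almost completely.

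**The case against.** The strongest reply has four parts.

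*"Withdrawn" may mean only consent withdrawn.* The wording allows this. The protocol also gives a milder route for conventional-arm patients on high FiO2 or PEEP, whose target can be modified temporarily without leaving the study, and it sends non-adherence to a per-protocol analysis. So the exclusion of medically withdrawn patients is an ambiguity, not a stated rule. That stands, and it is itself a reason to define the term.

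*Differential exclusion is not shown.* This also stands. A reader might infer that the primary contrast is biased because exclusion depends on the outcome. The documents do not support that: bias under the null needs exclusion that differs by arm. The open-label design makes this possible, but nothing in the text shows that it happens. A reader might also infer that a third or more of the 6-point target is at risk. That requires the upper-bound formula, both mechanisms in opposite arms, a fourfold difference in refusal and more exclusions than planned.

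*Only survivors leave.* Not quite. Proxies are approached early, and a refusal also removes some patients who later die. That halves the consent effect in the example above. The reason given for keeping deaths before consent is a Dutch committee's position, while consent follows local law and the trial also runs in Italy.

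*Removing refused data may be a legal duty, and reporting detail belongs in an analysis plan that is not shown.* Both are fair. No criticism is made of legally required removal or of unlisted tables. What remains is a rule that this article does state, under a label that it does not meet, in conflict with its own consent section.

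**Conclusion.** The point holds as a defect in the definition of the primary analysis set. The consent, withdrawal and analysis sections cannot all be applied as written. On the reading that follows the consent section, exclusion after randomisation can depend on vital status and, in an open-label trial, on knowledge of the arm. Neither planned robustness check is built to reveal this.

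The effect on the contrast is conditional. At 24% true mortality in both arms and the assumed rates, consent exclusions of 2% versus 8% produce at most about 1.2 points, or about 0.6 if half the deaths follow the consent request. Withdrawing 3% of one arm at 60% mortality produces about 1.1 points. Milder imbalances give less than 1 point, and equal exclusion gives none under the null. These are modest against 6 points, but exclusions within the planned 4% dropout could still raise the false-positive rate to about 8%. The sample size is not in question.

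**What to change.** Under Primary outcome {20a}:

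- Define the primary set as all randomised patients in their assigned arm. Exclude only those whose consent was refused or withdrawn and whose data may not legally be used.
- State that patients who die before consent is obtained are kept, in line with {26a} and local law in each country.
- State that patients withdrawn by the investigator stay in their assigned arm with 28-day vital status. Complete the unfinished sentence in {11b} so that leaving the study and leaving the analysis are distinguished.
- Add a best/worst-case sensitivity analysis over all excluded randomised patients by arm, whatever the missing fraction, so that it does not hang on the 5% trigger.

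The cost is wording and one extra sensitivity table. Vital status at day 28 is already the primary endpoint. N stays at 1512: with all 756 per arm analysed, power for 24% versus 18% is 81.8%, against 80.2% after 4% loss.

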#### Secondary outcome

Secondary endpoints that fall under the category of continuous normally distributed variables will be expressed as frequencies and percentages. Differences between groups in continuous normally distributed variables will be expressed by their means and standard deviations or when not normally distributed, as medians and their interquartile ranges. Secondary endpoints that fall under the category of categorical variables will be expressed as frequencies and percentages. Differences between groups in continuous variables will be analyzed with Student’s *t* test or, if continuous data is not normally distributed, the Mann-Whitney *U* test will be used. Categorical variables will be compared with the chi-squared test or Fisher’s exact test, as appropriate. Statistical significance is considered to be at a *p*-value < 0.05 with a two-sided test. When appropriate, statistical uncertainty will be expressed by 95% confidence levels. In addition to the unadjusted *p*-values for secondary outcomes, a procedure will be applied to control for multiple testing.

All statistical analyses will be performed with the R language and environment for statistical computing (R Foundation for Statistical Computing, Vienna, Austria).

### Interim analyses {21b}

No planned interim analysis will be performed. The data safety monitoring board (DSMB) will analyze a proxy endpoint, in-hospital mortality, for subject safety.

The stopping guidelines are defined as follows: The primary endpoint will be analyzed for safety reasons if a difference in in-hospital mortality of > 6% is found with a *p*-value < 0.005 (chi-square test). The study will only be stopped early for safety reasons if a difference in primary endpoint (28-day mortality) is found of > 6% with a *p*-value of < 0.001.

### Methods for additional analyses (e.g., subgroup analyses) {20b}

Subgroup analyses are planned to investigate the effects of oxygenation targets on the primary endpoint in the following subgroups: ARDS at ICU admission, patients with sepsis as reason for admission, patients with stroke, patients with myocardial infarction, and patients with elevated plasma lactate (> 2 mmol/l).

### Methods in analysis to handle protocol non-adherence and any statistical methods to handle missing data {20c}

Analysis will primarily be performed following the intention-to-treat principle. To handle protocol non-adherence, a secondary per-protocol analysis will be performed.

No or minimal losses to follow-up for the primary outcome is anticipated. Complete-case analysis will be carried out for all the outcomes. However, if more than 5% of missing data is found for the primary outcome, a sensitivity analysis using multiple imputations will be carried out.

### Plans to give access to the full protocol, participant-level data, and statistical code {31c}

The full protocol will be publicly accessible. Upon reasonable request, the dataset and statistical code will be made available.

## Oversight and monitoring

### Composition of the coordinating center and trial steering committee {5d}

The coordinating center and steering committee will provide trial oversight and is composed of the principal investigator, leading investigators, and experts of ventilation who contributed to the design and revision of the study protocol. The leading investigators are responsible for the daily management of the trial and provide assistance to participating ICUs in training in study-related procedures for the local staff, trial management, data management, and monitoring. Local investigators in each site will screen the patients who require mechanical ventilation and check if they are eligible for participation, perform randomization, supervise data collection, and ensure adherence to the ICH-GCP guidelines during the trial.

### Composition of the data monitoring committee, its role and reporting structure {21a}

An independent Data Safety and Monitoring Board (DSMB) watches over the ethics of conducting the study in accordance with the Declaration of Helsinki and monitors safety parameters and the overall conduct of the study. The DSMB is composed of three independent individuals. The DSMB will meet at least yearly. No competing interests were reported by the DSMB.

### Adverse event reporting and harms {22}

Adverse events (AE) are defined as any undesirable experience occurring to a subject during the study, whether or not considered related to the trial procedure and intervention strategies. Since this is a low-risk study in critically ill patients, comparing two currently used PaO_2_ targets, additional undesirable events related to the study protocol are not anticipated. Therefore, we will only register serious adverse events (SAEs) and will not record AEs.

Because this is a study in critically ill patients, SAEs are expected to occur frequently. Therefore, the following SAEs are not considered untoward in this population and will not be treated as SAE:
Death not related to the study interventionInfectionsBleedingOrgan failure

The following events occurring during ICU admission will be treated and registered as SAE:
PaO_2_ ≤ 5 kPa (37.5 mmHg)Ischemic events (limbs, cerebral, myocardial, intestinal)In-hospital cardiac arrest (IHCA)SpO_2_ < 80% for longer than 10 min (not explained by technical failure)Death possibly related to the study intervention

The site investigator will report all SAEs to the leading investigator without undue delay after obtaining knowledge of the events.

The sponsor or lead investigator will report the SAEs through the web portal to the accredited ethical reviewing board that approved the protocol, within 7 days of first knowledge for SAEs that result in death or are life threatening followed by a period of maximum of 8 days to complete the initial preliminary report. All other SAEs will be reported within a period of maximum 15 days after the sponsor has first knowledge of the serious adverse events.

